### Adverse event management

Adverse events (AE) are defined as *any untoward medical occurrence in a clinical trial subject and which do not necessarily have a causal relationship with the treatment*. All AEs will be listed on the appropriate Case Report Form for routine return to the ‘WOLLF’ central office.

Serious AEs are defined as any *untoward and unexpected medical occurrence that:*
Results in deathIs life-threateningRequires hospitalisation or prolongation of existing inpatients´ hospitalisationResults in persistent or significant disability or incapacityIs a congenital anomaly or birth defectAny other important medical condition which, although not included in the above, may require medical or surgical intervention to prevent one of the outcomes listed.

All serious AEs (SAE) will be entered onto the SAE reporting form and faxed to the dedicated fax system at WMSCTU within 24 h of the investigator becoming aware of them. Once received, causality and expectedness will be confirmed by the Chief Investigator. SAEs that are deemed to be unexpected and related to the trial will be notified to the Research Ethics Committee (REC) within 15 days. All such events will be reported to the TSC and Data Monitoring Committee (DMC) at their next meetings.

SAEs that may be expected as part of the surgical interventions and which do not need to be reported to the main REC are: complications of anaesthesia or surgery (wound infection, bleeding or damage to adjacent structures such as nerves, tendons and blood vessels, delayed unions/non-unions, delayed wound healing, further surgery to remove/replace metal-work and thromboembolic events). All participants experiencing SAEs will be followed-up as per protocol until the end of the trial.

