#### Risks and benefits

The risks associated with this study are predominantly the risks associated with the injury and the surgery: infection, bleeding and damage to the adjacent structures such as nerves, blood vessels and tendons. Participants in both groups will undergo surgery and will potentially be at risk from any/all of these complications. Allocation of the trial intervention will take place at the end of the initial surgery so that there is no difference between the groups in terms of surgical risk.

Both standard wound dressings and NPWT have been used widely in the civilian and military settings, and there are no specific risks associated with the use of either type of wound management—other than a potential reduction in the rate of wound complications, which is the focus of this trial.

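### The SAE definition requires an event to be unexpected, yet the same section lists expected SAEs, so 24 h reporting and the route to the DMC are unclear for serious wound complications

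*Protocol article*

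**What the plan says.** All statements are in the protocol article, mostly under Adverse event management.

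- An adverse event is any untoward occurrence, with no condition on expectedness. "All AEs will be listed on the appropriate Case Report Form for routine return".
- A serious adverse event is any "untoward and unexpected medical occurrence" that meets one of the usual seriousness criteria.
- "All serious AEs (SAE) will be entered onto the SAE reporting form" and faxed within 24 h of the investigator learning of the event. After receipt, "causality and expectedness will be confirmed by the Chief Investigator".
- The rule for telling the ethics committee is this: "SAEs that are deemed to be unexpected and related to the trial will be notified to the Research Ethics Committee (REC) within 15 days". The next sentence reads: "All such events will be reported to the TSC and Data Monitoring Committee (DMC) at their next meetings".
- A further paragraph lists "SAEs that may be expected as part of the surgical interventions and which do not need to be reported to the main REC". The list includes wound infection, bleeding, delayed or failed union, delayed wound healing, surgery to remove or replace metal-work, and thromboembolism.

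Under Risks and benefits the article adds: "The risks associated with this study are predominantly the risks associated with the injury and the surgery: infection, bleeding", together with damage to adjacent structures. It names wound complications as what the trial is about.

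**The concern.** Seriousness and expectedness are separate attributes. Seriousness decides whether an event enters the rapid reporting stream. Expectedness, with relatedness, usually decides only whether an ethics committee must be told quickly. Building expectedness into the definition merges the two, and the rest of the section then treats them as separate.

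Two practical matters depend on this. The first is whether a site must file an SAE form within 24 h for, say, a life-threatening wound infection. The second is whether the DMC is told of such events. Infection, bleeding and delayed healing are the events most directly tied to the choice of dressing, so they are the ones for which the rule most needs to be clear.

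**Working it through.** No arithmetic applies, because the point concerns a definition and a reporting route. The check sets the statements side by side.

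**Step 1: is there a contradiction?**

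- The definition admits an event as an SAE only if it is unexpected.
- The Chief Investigator confirms expectedness after the form arrives. That step has a purpose only if expected SAEs can arrive.
- The ethics committee rule selects SAEs that are unexpected and related. The word unexpected would be redundant there if every SAE were already unexpected.
- The last paragraph names a class of expected SAEs. Under the definition that class is empty.

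Three later statements therefore assume what the definition rules out. The adverse event definition carries no such condition, so the restriction enters only at the serious level.

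**Step 2: what follows for the SAE form?**

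- Under the definition, a serious wound infection is on the expected list, so it is not an SAE and needs no form within 24 h.
- Under the last paragraph, the same infection is an SAE. It goes on the form within 24 h and is exempt only from reporting to the main ethics committee.

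Both readings come from the same section. The literal one also moves the judgement of expectedness to the site, before any report is made. The Blinding section says the treating surgeons know the allocation, although it also gives them no part in postoperative assessment. The article does not say who at the site would make this judgement.

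**Step 3: what reaches the DMC?**

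The sentence "All such events will be reported to the TSC and Data Monitoring Committee (DMC) at their next meetings" directly follows the one on unexpected, related SAEs, and that is its natural antecedent. No other sentence in the article sends SAEs to the DMC. The Oversight section sets up a TSC and a DMC but mentions written reports for the TSC only. The Main RCT analysis section provides interim analyses only if the DMC directs them. Expected serious events therefore have no stated route to the DMC.

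**Step 4: are the events recorded elsewhere?**

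Yes.

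- All adverse events go on the case report form.
- Deep infection is a secondary outcome, with blinded review of photographs and X-rays.
- Complications and surgical interventions related to the fracture are recorded as outcomes (Outcome measures).
- The Follow-up section collects complications at 6 weeks, at 3, 6, 9 and 12 months by questionnaire, and at the 12-month review.
- Deep infection and other complications are compared between arms by mixed effects logistic regression (Main RCT analysis).

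None of these is stated to work on a 24 h timescale, and none is stated to go to the DMC during recruitment.

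**The case against.** The strongest reply is that one word should not outweigh the rest of the section. The operative text calls the listed events SAEs, sends all SAEs to the form, judges expectedness only on receipt, and gives a single express exemption, which is from the main ethics committee. A sensible site would probably file the form. This stands as a reason not to treat the exclusion as settled. It does not remove the contradiction, because the definition is what a site consults to decide whether a form is due.

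Three stronger readings are tempting, and the documents do not support them.

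- A reader might infer that serious infections and bleeding are simply outside the SAE category and need not reach the DMC. No sentence exempts them from the DMC. The narrow reach is inferred from an ambiguous pronoun phrase, and it sets a minimum rather than a limit on what the DMC may see. The content of DMC reports may also sit in a charter or full protocol that is not shown.
- A reader might infer that all re-operations are affected. The only re-operation the expected list names is surgery to remove or replace metal-work.
- A reader might size the gap by applying the quoted 27% infection risk to the 460 participants. The Introduction ties that figure to severe, high-energy fractures, whereas grade 2 wounds are also eligible. It also counts infections in general, not those meeting a seriousness criterion.

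**Conclusion.** The Adverse event management section is wrong as written. Its definition of an SAE cannot be reconciled with its own provisions for expected SAEs. Applied literally, the definition takes serious wound infection, bleeding, delayed healing and metal-work surgery out of 24 h reporting. The only stated route to the DMC most naturally covers unexpected, related SAEs alone.

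The consequence is inconsistent SAE reporting and an unclear safety flow to the DMC, not loss of data. The sample size and the primary analysis are unaffected. No count can be attached, since the article gives no rate of serious complications.

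The contradiction rests on the article's text alone. The DMC part rests on the natural antecedent of one sentence, and unseen DMC documents could soften it. The point is worth correcting for safety monitoring, but it does not threaten the validity of the trial.

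**What to change.** Make three wording changes under Adverse event management:

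1. Delete *and unexpected* from the SAE definition, so that seriousness alone makes an event an SAE and triggers the form within 24 h.
2. Let expectedness, together with relatedness, govern notification of the ethics committee only. The list of expected events then keeps its stated purpose.
3. Replace the opening of the sentence on TSC and DMC reporting so that it says all SAEs, including the listed expected ones, are reported to both committees. The layout of the DMC tables can stay in a charter.

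The cost is a wording amendment, matching guidance for completing the case report form, and modestly more SAE forms at sites for events they already record as complications.

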#### Risks and benefits

The risks associated with this study are predominantly the risks associated with the injury and the surgery: infection, bleeding and damage to the adjacent structures such as nerves, blood vessels and tendons. Participants in both groups will undergo surgery and will potentially be at risk from any/all of these complications. Allocation of the trial intervention will take place at the end of the initial surgery so that there is no difference between the groups in terms of surgical risk.

Both standard wound dressings and NPWT have been used widely in the civilian and military settings, and there are no specific risks associated with the use of either type of wound management—other than a potential reduction in the rate of wound complications, which is the focus of this trial.

### End of trial

The end of the trial will be defined as the collection of 1-year outcome data from the last participant.

### Oversight

We will institute a rigorous programme of quality control. Quality assurance checks will be undertaken by Warwick CTU to ensure integrity of randomisation, study entry procedures and data collection. The Warwick CTU has a quality assurance manager who will monitor this trial by conducting regular (yearly or more, if deemed necessary) inspections of the Trial Master File. Furthermore, the processes of consent taking, randomisation, registration, provision of information and provision of treatment will be monitored. A TSC and a DMC will be set up. Written reports will be produced for the TSC, informing them if any corrective action is required.

## Statistical analysis

### Feasibility study

At the end of the feasibility phase, the overall mean recruitment at the five selected centres for this phase of the study will be estimated (with a 95% CI) and compared to the target rate of one patient per month per centre. The estimated recruitment rate and the overall rate of withdrawn patients in the feasibility phase will inform the design and the decision to proceed to the main RCT.

### Main RCT

Standard statistical summaries (eg, medians and ranges or means and variances dependent on the distribution of the outcome) and graphical plots showing correlations will be presented for the primary outcome measure and all secondary outcome measures. Baseline data will be summarised to check comparability between treatment arms, and to highlight any characteristic differences between those individuals in the study, those ineligible and those eligible, but withholding consent.

The main analysis will investigate differences in the primary outcome measure, the DRI score at 1 year after injury, between the two treatment groups (standard wound dressings and negative pressure wound therapy) on an intention-to-treat basis. In addition, early functional status will also be assessed and reported at 3, 6 and 9 months. Differences between groups will be assessed, based on a normal approximation for the DRI score at 12 months postinjury and at interim occasions. Tests will be two sided and considered to provide evidence for a significant difference if p values are less than 0.05 (5% significance level).

The stratified randomisation procedure should ensure a balance in Gustilo and Anderson grade and the recruiting centre's between-test treatments. Although generally we have no reason to expect that clustering effects will be important for this study, in reality, the data will be hierarchical in nature, with patients naturally clustered into groups by the recruiting centre. Therefore, we will account for this by generalising the conventional linear (fixed effects) regression approach to a mixed effects modelling approach, where patients are naturally grouped by recruiting centres (random effects). This model will formally incorporate terms that allow for possible heterogeneity in responses for patients due to the recruiting centre, in addition to the fixed effects of the treatment groups, Gustilo and Anderson grade, and other patient characteristics that may prove to be important moderators of the treatment effect such as age and gender.

It seems likely that some data may not be available due to voluntary withdrawal of patients, lack of completion of individual data items or general loss to follow-up. Where possible, the reasons for data ‘missingness’ will be ascertained and reported. Although missing data is not expected to be a problem for this study, the nature and pattern of the missingness will be carefully considered—including, in particular, whether data can be treated as missing completely at random. If judged appropriate, missing data will be imputed, using the multiple imputation facilities available in R (http://www.r-project.org/). The resulting imputed datasets will be analysed and reported, together with appropriate sensitivity analyses. Any imputation methods used for scores and other derived variables will be carefully considered and justified. Reasons for ineligibility, non-compliance, withdrawal or other protocol violations will be stated and any pattern observed will be summarised. More formal analysis, for example, using logistic regression with ‘protocol violation’ as a response, may also be appropriate and aid interpretation. About 1–2% of patients are expected to die during follow-up; so this is unlikely to be a serious cause of bias. However, we will conduct a secondary analysis taking account of the competing risk of death, using methods described by Varadhan *et al*.^22^

The main analyses will be conducted using specialist mixed effects modelling functions available in the software package R (http://www.r-project.org/) where DRI data will be assumed to be normally distributed, possibly after appropriate variance stabilising transformation. The primary focus will be the comparison of the two treatment groups of patients, and this will be reflected in the analysis which will be reported together with appropriate diagnostic plots that check the underlying model assumptions. Results will be presented as mean differences between the trial groups, with 95% CIs.

Secondary analyses will be undertaken using the above strategy for approximately normally distributed outcome measures SF-12 and EQ5D. For dichotomous outcome variables, such as indicators of deep infection and other complications related to the trial interventions, mixed effects logistic regression analysis will be undertaken with results presented as ORs (and 95% CIs) between the trial groups. Also, temporal patterns of any complications will be presented graphically and if appropriate, a time-to-event analysis (Kaplan-Meier survival analysis) will be used to assess the overall risk and risk within individual classes of complications.

A detailed statistical analysis plan (SAP) will be agreed on with the DMC. Any subsequent amendments to this initial SAP will be clearly stated and justified. Interim analyses will be performed only where directed by the DMC. The routine statistical analysis will mainly be carried out using R (http://www.r-project.org/) and S-PLUS (http://www.insightful.com/*).* Results from this trial will also be compared with results from other trials.

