### Sample size

The minimum clinically important difference (MCID) for the primary outcome measure (DRI) is assumed to be eight points.^13^ The DRI is a 12-item, patient-reported, functional outcome questionnaire that is transformed to a 100 point scale, where 0 represents normal function and 100 complete disability. At an individual patient level, a difference of eight points represents the ability to climb stairs or run with ‘some difficulty’ versus with ‘great difficulty’. At a population level, eight points represents the difference between a ‘healthy patient’ and a ‘patient with a minor disability’.

In table 1, the bold figure of 412 patients represents a conservative scenario, based on a SD of 25 and 90% power to detect the selected MCID. However, a sample size of 308 patients would still provide 80% power. Allowing a margin of 10% loss during follow-up, including the small number of patients who die in the first year following their injury, this gives a figure of *460* patients in total. Therefore, 230 patients who consent to each group will provide 90% power to detect a difference of eight points in DRI at 12 months at the 5% level.

**Table 1 BMJOPEN2015009087TB1:** Sample size for varying power and SD

SD	Power	
	80%	90%
15	112	150
20	198	264
25	308	**412**

The sample size used in the trial is shown in bold.

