#### Randomisation

The allocation sequence will be generated by an independent randomisation centre—York CTU. Randomisation will be on a 1:1 basis, stratified by trial centre and Gustilo and Anderson grade—2, 3, or 3 with vascular injury requiring surgical repair. Eligibility for the trial is based on a wound of grade 2 or above, which will be established definitively at the end of the initial surgical debridement in the operating theatre as per routine clinical practice. Therefore, participants will be assigned to their treatment allocation at the end of the initial surgery, but before the wound dressing is applied. All modern operating theatres include a computer with web-access; so a secure, 24 h, web-based randomisation system will be used to generate the treatment allocation intraoperatively.

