#### Follow-up

Baseline, standardised radiographs will be copied onto CD from the hospital PACs (archiving) system. Copies of the baseline clinical report forms and CD will be delivered to the trial coordinating centre.

The research associate will make a record of any early complications at the routine 6-week follow-up appointment and take a photograph of the wound. This data will be returned to the trial coordinating centre, together with a copy of the routine 6-week follow-up radiograph. The number and timing of any subsequent follow-up appointments will be at the discretion of the treating surgeon. All patients will be reviewed at 12 months as per routine practice after this type of injury. Details of any late complications and copies of the 12-month radiographs will be sent to the trial coordinating centre.

The functional outcome data will be collected using questionnaires at 3, 6, 9 and 12 months postoperatively (see table 2). In addition to the DRI, the patients will be asked to fill out the EuroQol and SF-12 questionnaires, and a complications/further surgical interventions and health economics questionnaire. The 3, 6 and 9 months postoperative questionnaires will be sent to the patients by post, a process done centrally by a data clerk at the Warwick CTU. All of the outcome questionnaires can be completed over the phone if postal copies are not returned. Patients will be asked to complete their 12 months postoperative questionnaire during their routine follow-up appointment 1-year postoperation.

**Table 2 BMJOPEN2015009087TB2:** Follow-up measures

Time point	Data collection
Baseline	DRI and SF-12 preinjury, EQ-5D preinjury and contemporary, routine radiographs of leg wound(s)
6 weeks	Complication records, radiographs, operative record, photograph of leg wound(s)
3 months	DRI, EQ-5D, SF-12 record of complications/rehabilitation or other interventions, and economics questionnaire
6 months	DRI, EQ-5D, SF-12 record of complications/rehabilitation or other interventions, and economics questionnaire
9 months	DRI, EQ-5D, SF-12 record of complications/rehabilitation or other interventions, and economics questionnaire
12 months	DRI, EQ-5D, SF-12 record of complications/rehabilitation or other interventions, and economics questionnaire, radiographs

DRI, Disability Rating Index.

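### The primary model's covariate list is left open and described as treatment-effect moderators, and it does not say whether the pre-injury DRI scheduled at baseline is included

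*Protocol article*

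**What the plan says.** Under Statistical analysis, Main RCT, the protocol article fixes the endpoint: "The main analysis will investigate differences in the primary outcome measure, the DRI score at 1 year after injury". The comparison is by intention to treat, two-sided at 5%. The model is a linear mixed model with recruiting centre as a random effect. Its fixed effects are treatment, Gustilo and Anderson grade, and "other patient characteristics that may prove to be important moderators of the treatment effect such as age and gender". The result is to be reported as a mean difference between groups with a 95% CI. The same strategy is then applied to SF-12 and EQ-5D.

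The baseline row of Table 2 (Follow-up) schedules "DRI and SF-12 preinjury, EQ-5D preinjury and contemporary, routine radiographs of leg wound(s". The analysis section does not mention the pre-injury scores. On allocation, the Randomisation section says "Randomisation will be on a 1:1 basis, stratified by trial centre and Gustilo and Anderson grade", with three grade levels: 2, 3, and 3 with a vascular injury needing repair.

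The Main RCT section also says that a detailed SAP will be agreed with the DMC. That SAP is not at hand.

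**The concern.** The covariate clause has three weaknesses.

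- **It is conditional.** Characteristics enter if they turn out to matter. Read naturally, this lets the trial's own data decide which terms are in the model that yields the primary p-value.
- **It is open.** Age and gender are examples, so a reader cannot write down the primary model from the text.
- **It names the wrong role.** A moderator changes the size of the treatment effect and is modelled as a treatment-by-covariate interaction. A prognostic covariate predicts outcome and is modelled as a main effect. The clause calls these terms moderators but lists them among the fixed effects of the main model. If they were entered as interactions, the treatment coefficient would depend on how the covariates are coded and would not in general be the single mean difference the section promises.

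Alongside this, the pre-injury value of the outcome itself is scheduled but its place in the model is not stated. Eligibility starts at age 16 with no upper limit, so pre-injury function may vary and may predict 12-month DRI. At stake are the pre-specification of the primary test and some precision. The stated power is not at risk.

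**Working it through.** **Inputs from the protocol article.** Difference 8 points ("The minimum clinically important difference (MCID) for the primary outcome measure (DRI) is assumed to be eight points"). SD 25, 90% power and 412 analysed patients ("the bold figure of 412 patients represents a conservative scenario, based on a SD of 25 and 90% power to detect the selected MCID"). Two-sided 5% test, 1:1 allocation, 10% loss.

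**Input not in the document.** The correlation r between pre-injury and 12-month DRI. It is an assumption here, shown from 0 to 0.6.

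**Step 1: reproduce the plan's figures.** n per arm = 2 × SD² × (1.960 + 1.282)² / 8² = 2 × 625 × 10.51 / 64 = 205.2, rounded up to 206, so 412 in total. Allowing for loss, 412 / 0.90 = 457.8, or 458, against the stated 460. Both agree, and neither uses covariate adjustment.

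**Step 2: effect of adding pre-injury DRI, against an unadjusted analysis.** Residual SD = 25 × √(1 − r²). SE = residual SD × √(2/206). Power = Φ(8/SE − 1.96). CI half-width = 1.96 × SE. At r = 0, SE = 25 × √(2/206) = 2.463, 8/2.463 = 3.248, and Φ(1.288) = 90.1%.

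| assumed r | variance removed (r²) | SE ratio | power, 206 per arm | 95% CI half-width (points) | total N for 90% power |
|---|---|---|---|---|---|
| 0 | 0% | 1.000 | 90.1% | 4.83 | 412 |
| 0.1 | 1% | 0.995 | 90.4% | 4.80 | 408 |
| 0.2 | 4% | 0.980 | 91.2% | 4.73 | 396 |
| 0.3 | 9% | 0.954 | 92.6% | 4.61 | 374 |
| 0.4 | 16% | 0.917 | 94.3% | 4.43 | 346 |
| 0.5 | 25% | 0.866 | 96.3% | 4.18 | 308 |
| 0.6 | 36% | 0.800 | 98.2% | 3.86 | 264 |

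The gain is negligible at r = 0.1 to 0.2 and material from about 0.4.

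**Step 3: the comparator.** The table compares with no adjustment at all. The planned model already holds grade and centre, and may hold age and gender. The added gain over that model is governed by the partial correlation of pre-injury DRI with 12-month DRI given those terms. If age carries part of the same information, the partial correlation is lower than r and the gain is smaller.

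**Step 4: how far free selection could matter.** This is an upper-end illustration under no treatment effect, with 412 patients, 2,000 simulated trials per setting and independent candidate covariates. Every subset of candidates was fitted and the most significant treatment test kept.

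| candidates | each correlated 0.2 with outcome | each correlated 0.3 with outcome |
|---|---|---|
| 2 | 6.9% | 8.5% |
| 3 | 8.1% | 10.8% |
| 4 | 8.8% | 13.3% |

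Without selection the simulated rate was 4.5% to 5.4%. The protocol does not say that covariates would be chosen on the treatment p-value, so these figures bound the room the wording leaves and do not forecast the trial's error rate.

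**The case against.** The strongest reply is that this is a condensed article with an SAP to follow. The final covariate list, including whether the baseline score enters, is commonly left to the SAP, and a list agreed with the DMC could be closed before any outcome is analysed. That stands as far as silence on pre-injury DRI goes: silence alone would not be a finding. It does not dispose of the clause itself, because the article states a principle for choosing covariates, and that principle is conditional and uses the wrong term.

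Several stronger readings are tempting but are not supported:

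- **That pre-injury DRI is left out of the analysis.** The list is open and could include it. It is unnamed, not excluded.
- **That every patient provides it.** Table 2 only schedules it. Some patients decline, withdraw or are excluded after randomisation.
- **That interactions will be in the primary model.** No interaction term is written, and the section says the primary focus is the comparison of the two groups. The harm to the treatment coefficient arises only if the word moderators is taken literally.
- **That covariates will be picked on the data.** The wording permits this, but no selection procedure is stated.
- **That adjustment has no downside.** Allocation is made in theatre and most patients are expected to lack capacity before surgery, so for most the pre-injury score will be recalled after allocation. Patients are not blinded, and recall could differ by arm.

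The size of the gain is also uncertain. Zero on the DRI is normal function, so pre-injury scores may cluster near zero and correlate weakly with 12-month disability.

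**Conclusion.** The point holds as a fault in a stated method. The clause defining the primary model should be replaced, because as written the model is not fixed and prognostic covariates are not separated from effect modifiers. Whether pre-injury DRI enters should be settled in the same sentence.

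The benefit from pre-injury DRI is precision only. Against an unadjusted analysis with 206 per arm, power moves from 90.1% to between 90.4% (r = 0.1) and 96.3% (r = 0.5), and the CI half-width from 4.83 to between 4.80 and 4.18 points. These figures rest on the protocol's SD of 25 and difference of 8, and on a correlation the document does not give. Over a model already holding grade, age and gender the gain may be smaller. A reader might infer that the trial is underpowered without this term. It is not, since 412 reproduces with no adjustment. The unseen SAP may already close the list, in which case only the article's wording needs to be brought into line.

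**What to change.** Replace the covariate clause with a closed model, set before outcome data are seen:

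- **Primary model:** 12-month DRI on treatment, pre-injury DRI, Gustilo and Anderson grade at its three randomisation levels, age and gender, all as main effects, with centre as a random effect.
- **SF-12 and EQ-5D:** the same model, using the pre-injury value of the outcome concerned.
- **Interactions:** treatment-by-covariate terms only in separate, named subgroup analyses.
- **Missing pre-injury score:** keep the patient by a simple imputation, for example the overall mean, so that adjustment does not shrink the analysed group.
- **Sensitivity analysis:** the same model without pre-injury DRI, because for most patients the score is recalled after allocation in an unblinded trial.

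The cost is protocol and SAP wording and one extra reported model. The data are already scheduled for collection and the sample size does not change. The small downside is reliance on a recalled score, which the sensitivity analysis addresses.
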